# 0. Summary

## Scheme

Major eligibility criteria

・Type 2 diabetes aged 20-80 years

・HbA1c 6.5～10.0%

・BMI 20～34kg/m^2^

Judgment of effectiveness, after 20 weeks of the study

Physical fitness test, Imaging test (CT, MRI), Blood glucose variability assessment

Start of the trial (Start of interval walking training)

In principle, visits every 4 weeks, blood and urine tests will be performed.

20週間

Registration

Target number of enrollment cases：70

Period of case enrollment：After the ethics committee recognized～December 31th, 2019

After registration

Physical fitness test, Imaging test (CT, MRI), Blood glucose variability assessment

## Objective and significance

## To evaluate the usefulness of interval walking training (IWT) for patients with type 2 diabetes in terms of improved glycemic control and changes in body composition (changes in body weight, body fat, liver fat, muscle mass, etc.).

## Target

・Type 2 diabetes patients aged 20-80 years

・HbA1c 6.5～10.0%

・BMI 20～34kg/m^2^

## Target enrollment and duration of research

Target number of enrollment cases：70 cases of IWT

Period of case enrollment：From after the ethics committee recognized to December 31th, 2019

Test period：From after the ethics committee recognized to December 31th, 2020

## Research design

Design features：Single-arm intervention studies

Type of control：none

Randomization：none

Type of blinding：none

## Assessment item

## **Primary endpoint**：Changes in HbA1c levels from baseline (at start) to 20 weeks

## **Secondary endpoints**：Liver fat content by MRI, Abdominal visceral fat and thigh muscle mass by CT, Thigh muscle strength using a muscle testing device, BMI, VO2 peak (maximal oxygen uptake), insulin sensitivity (blood C-peptide, IRI), HDL cholesterol, LDL cholesterol, Triglycerides, Systolic blood pressure, Mean blood glucose and blood glucose variability (using of FreeStyle Libre Pro), Urine albumin, Change in drug dose from baseline (at start) to 20 weeks, Frequency of IWT and achievement rate of the target length of IWT (at least 60 minutes/week of fast walking)

### **Safety endpoints**：Adverse events (hypoglycemia and hypotension), Serious adverse events, Survey on locomotor disorders

## Contact information

【Inquiries about test content】

Research Office：Fourth Department of Internal Medicine, Shinshu University School of Medicine

　[name]

　TEL：[contact]，FAX：[contact]

# Objective and significance

To evaluate the usefulness of IWT for patients with type 2 diabetes in terms of improved glycemic control and changes in body composition (changes in body weight, body fat, liver fat, muscle mass, etc.).

# 2. Background and rationale

In a survey by the Ministry of Health, Labor and Welfare in Japan, the estimated number of adults with suspected diabetes increased to 10 million in 2016, and diet and exercise therapy are important for prevention and treatment of type 2 diabetes.

It has been reported that exercise therapy in diabetes patients improved insulin resistance in skeletal muscle and also reduced liver fat mass^1^.

It has also been suggested that exercise therapy is effective in improving HbA1c levels in patients with diabetes (Aerobic exercise group showed -0.46% reduction in HbA1c compared to the control group, resistance exercise group showed -0.37% reduction in HbA1c compared to the control group, and aerobic exercise group + resistance exercise group showed -0.96% reduction in HbA1c compared to the control group)^2^.

With alarming of sarcopenia (muscle weakness) in patients with diabetes, exercise therapy is important even for elderly diabetic patients. In reality, the implementation rate of exercise therapy is low. This is due to a variety of reasons, including patient motivation, time constraints, and lack of habit. Further, it is difficult for medical professionals to instruct patients on exercise therapy because there is no well-established method of exercise therapy for patients with diabetes. IWT "(walking at 70% or more of maximum fitness and walking at 40% or less of maximum fitness alternately for 5 to 10 sets/day for 3 minutes each, repeated at least 4 days/week)" is established by the Department of Sports Medical Sciences, Shinshu University Graduate School of Medicine. There is a report that IWT in patients with diabetes resulted in weight loss (-0.7 kg in a general exercise therapy group and -4.2 kg in IWT group) and a decrease in average blood glucose in CGM (+2 mg/dl in a general exercise therapy group and IWT group -12 mg/dl)^3^. One of the reasons for the effectiveness is the high level of adherence. Another reason may be that IWT allows patients to perform both aerobic and resistance exercise at the same time^4^。

However, there are no papers in Japan evaluating the effectiveness of IWT for patients with type 2 diabetes mellitus.

Therefore, we would like to evaluate blood glucose control and changes in body composition in patients with type 2 diabetes by performing IWT.

We would also like to examine the required amount of IWT to achieve the goal of HbA1c less than 7% in patients with diabetes.

# 3. Summary of test drugs

# Not applicable for this study.

# 4. Criteria for eligibility

# Patients who meet all of the following selection criteria and none of the following exclusion criteria will be considered eligible for enrollment.

## 4.1.　 Selection criteria

1. Type 2 diabetes aged 20-80 years at the time of informed consent.
2. HbA1c 6.5～10.0%
3. BMI 20～34kg/m^2^
4. Patients who have given full explanation of their participation in this study and who have given written consent of their own free will.
5. Patients who are considered by their physician to be eligible for exercise therapy.

## 4.2.　 Exclusion criteria

1. Patients diagnosed with pre-diabetic proliferative or proliferative retinopathy.
2. Urinary albuminuria > 300 mg/gCre, or eGFR < 30 mL/min/1.73 m^2^.
3. History of stroke.
4. History of coronary artery disease.
5. Patients considered inappropriate as participants by the principal investigator.

## 4.3. Subjects requiring consent by a surrogate and the reasons for such consent

Not applicable for this study.

# 5. Research methods

## 5.1.　 Research design

Design features：Single-arm interventional study

Type of control：none

Randomization：none

Type of blinding：none

## 5.2.　 Research outline

## The target enrollment number is 70 patients.

## After enrollment, patients will undergo physical fitness measurements, imaging tests (simple CT of the abdomen and the thighs, and simple MRI of the abdomen), and evaluation of blood glucose variability using FreeStyle Libre Pro, followed by 20 weeks of IWT.

## At the end of the 20 weeks, physical fitness tests, imaging tests, and FreeStyle Libre Pro will be performed to compare before and after IWT. Participants will be encouraged to continue IWT as much as possible until he/she completes the study.

## 5.3.　 How to perform an interventional study

## During the pre-observation period, the participants will undergo simple CT of the abdomen and thighs, and simple MRI of the abdomen, physical fitness tests sponsored by the Research Center of the University of Physical Education (hereinafter referred to as JTRC).

## On screening day, the participants will start to put on FreeStyle Libre Pro, take dietary survey, start to be measured for energy consumed in daily life using JD mate. After that, the participants will wear FreeStyle Libre Pro for 2 weeks, and JD mate for 1 week.

## When taking physical fitness tests, the participants will receive explanation of the content of IWT and be explained again how to handle JD mate.

## The participants will see the doctor on the start date of IWT. The target length of IWT is to walk 60 minutes/week for a total of 20 weeks. As a rule, the participants will be visited every 4 weeks during this period.

## At 18 weeks after the start of the study, FreeStyle Libre Pro will be worn for 2 weeks, and diet survey was performed at the same time. The participants will be also measured for energy consumed in daily life by wearing JD mate for one week.

Within 2 months after the completion of IWT, the patients will be required to undergo simple CT of the abdomen and thighs, simple MRI of the abdomen, and physical fitness tests.

< Details of IWT, the physical fitness tests, FreeStyle Libre Pro, and imaging tests are as follows. >

## Physical fitness test:

Physical fitness tests will be performed at the pre- and post-test observation periods. In this test, maximal oxygen uptake (physical fitness) measurements will be made. The items including physical fitness measurements are listed in the table below.

Measurements

【Morphometrics】

Height, weight, blood pressure, abdominal circumference

【physical fitness test】

Maximal oxygen uptake from walking, muscle strength

## Walking speed is gradually increased, and when reaching full strength, maximal oxygen uptake is measured.

## 2 IWT (Interval Walking Training)：

## Maximal oxygen uptake is the maximum amount of oxygen that an individual can be taken in per minute per kilogram of body weight (mg/kg/min). It is used as an indicator of body endurance (physical fitness).

## IWT is an exercise therapy in which fast walking (>70% of maximal oxygen uptake) and slow walking (<40% of maximal oxygen uptake) are performed for 3 minutes each, for a total of 5 sets (30 minutes)/day, at least 4 times a week. In this clinical trial, the target length of fast walking is set at 60 minutes/week. We would like to examine adherence to IWT, and so, except for participants who withdraw their consent, the study will continue even if the actual fast walking time is not enough. Eventually, all remaining participants will be evaluated after completion of the study. We will ask the participants to continue IWT as much as possible after the 20-week period until they have completed all the evaluation.

## During IWT, an accelerometer and barometer called "JD Mate" are used to estimate the amount of exercise and calories burned. When exercising while wearing this machine, the exercise record is tallied and the rhythm of the fast walking is also indicated with an audible sound.

## FreeStyle Libre Pro：

## This is a one of the continuous blood glucose monitors. When a small, round sensor is attached by a healthcare provider to the back of the upper arm, a very fine needle in the center of the sensor continuously measures glucose levels in the tissue interstitial fluid.

Since the retention period of data imported into JD mate is 2 weeks, we will evaluate the pre- and post-test blood glucose trends by wearing on JD mate at a 2-week pre-observation period and a 2-week period from week 18 to 20 of the study.

## Imaging tests：

## Liver fat will be determined by simple abdominal MRI. Visceral fat at the umbilical line and muscle mass at the center of the right thigh will be determined by simple CT. Muscle strength of the lower limbs will be quantified by the exercise function analyzer "zaRitzBM-220", and the "isometric lower limb muscle strength meter" during the physical fitness tests. These will be performed during the pre- and post-test observation periods, and we will evaluate changes in these items before and after the test (during the post-test observation period, we ask the participants to continue their exercise therapy until all tests have been performed).

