# 12. Completion and submission of case report forms

## 12.1.　 Forms and submission deadlines

Case report forms will be submitted by EDC (Electronic Data Capture System). The principal investigator, research assistant, and collaborator in charge will submit data using EDC as the study progresses. If the form is to be completed by someone other than the physician in charge, confirmation from the physician in charge will be obtained.

Reportable submission period

| No. | Type | Reporting Period |
| --- | --- | --- |
| 1 | Registration form | After obtaining consent |
| 2 | Case Report_Patient Background | Within 2 weeks of each scheduled visit |
| 3 | Case Report_Clinical Laboratory Data | Within 2 weeks of each scheduled visit |
| 4 | Case Report_Body Composition Assessment by Imaging Studies | Within 2 weeks of each scheduled visit |
| 5 | Case report_VO2 peak and isometric leg muscle strength measurements | Within 2 weeks of each scheduled visit |
| 6 | Case Report_Training | Within 2 weeks of each scheduled visit |
| 7 | Case Report_Daily Calorie Consumption | Within 2 weeks of each scheduled visit |
| 8 | Case Report_Concomitant medications | Within 2 weeks of each scheduled visit |
| 9 | Case Report_Adverse Events | Within 2 weeks of each scheduled visit |
| 10 | Musculoskeletal Disorders Questionnaire | Within 2 weeks of each scheduled visit |
| 11 | Case report_discontinued | Within 2 weeks of treatment discontinuation or dropout |

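### Masked or paired reading of the CT and MRI scans is not provided for, and baseline values are due before the post-test scan exists, so reader expectation cannot be excluded from the body-composition changes

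*Protocol*

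**What the plan says.** - **Design (Protocol 5.1, repeated in the Summary).** "Design features：Single-arm interventional study", "Type of control：none" and "Type of blinding：none". Image readers are not mentioned.
- **Imaging (Protocol 5.3, Imaging tests).** "Liver fat will be determined by simple abdominal MRI" and "Visceral fat at the umbilical line and muscle mass at the center of the right thigh will be determined by simple CT". On use of the results: "we will evaluate changes in these items before and after the test". The section gives the modality and, for CT, the anatomical level. It names no reader, software, region of interest, repeat read or masking.
- **Timing (Protocol 5.3 and the section 8 schedule).** The first body-composition assessment falls in the observation period before the start date. The second falls between weeks 20 and 28 after the start date.
- **Filing (Protocol 12.1, form 4).** "Case Report_Body Composition Assessment by Imaging Studies | Within 2 weeks of each scheduled visit".
- **Role of the endpoints.** Liver fat, visceral fat and thigh muscle are secondary endpoints (7.2). Change in body composition stands beside glycemic control in the objective. Section 11.2.3 plans descriptive summaries and exploratory modelling for secondary endpoints. A mean with a 95% confidence interval is specified only for HbA1c (11.2.2).

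**The concern.** Walking training cannot be blinded, but the reading of a stored image can. If whoever measures a scan knows whether it was taken before or after training, expectation may influence where a boundary or region is placed. In a randomized trial with both arms read the same way, much of such a shift would cancel. Here there is one arm and the result is the mean of post minus pre, so any average difference in reading between the two time points enters that mean in full. No later analysis of the same readings can separate it from an effect of training.

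The filing rule makes this more than silence. If form 4 is completed on time, the baseline value is fixed long before the second scan is taken, so the reported value cannot come from a paired, random-order read. The protocol does not provide for replacing it later. The matter concerns how measurements are made and filed, so it belongs in 5.3 and 12.1 and not among the statistical details that section 11 leaves to a separate plan.

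**Working it through.** **1. Order of events.** Take the baseline imaging visit as no later than the start date, as the section 8 schedule shows.
- Baseline form due: no later than week 0 + 2 = week 2.
- Post-test scan: weeks 20 to 28.
- Gap from due date to second scan: at least 20 − 2 = 18 weeks, and at least 28 − 2 = 26 weeks if the scan is taken at week 28.

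A read of both scans together therefore cannot be the source of a baseline value filed on time.

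**2. No stated figure to reproduce.** The target of 70 rests on feasibility (11.1). The protocol gives no SD of change, no effect size and no reading error for CT or MRI. What follows is a sensitivity illustration, with the shift assumed and expressed in units of the SD of the within-patient change.

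**3. Width of an interval, if one were reported.** For a mean paired change, the 95% half-width is t(0.975, n−1) × SD / √n.
- n = 70: 1.995 / 8.367 = 0.238 SD.
- n = 50 (assumed loss of 20 patients): 2.010 / 7.071 = 0.284 SD.

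**4. Chance that the interval excludes zero with no true change.** Let post-test readings be shifted on average by b SD. The t statistic then follows a noncentral t distribution with n−1 degrees of freedom and noncentrality b√n. The probability is P(T > t) + P(T < −t), where t is the 0.975 quantile used in step 3.

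| Assumed shift b (SD) | b√70 | n = 70 | n = 50 |
|---|---|---|---|
| 0 | 0 | 5% | 5% |
| 0.05 | 0.42 | 7% | 6% |
| 0.1 | 0.84 | 13% | 11% |
| 0.2 | 1.67 | 38% | 28% |
| 0.3 | 2.51 | 70% | 55% |

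A shift of 0.05 SD does little harm. From about 0.2 SD upward it could by itself often look like an effect. The point estimate moves by the full shift whether or not an interval is shown.

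**The case against.** The strongest reply has four parts.

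- **Reader knowledge is not stated.** A reader of the protocol might infer that scans are measured with the time point known. The documents do not say so. The blinding entry is a design-level item, and the table in 12.1 sets due dates without saying who reads a scan or what that person knows. This stands. What can be said is that nothing prevents it and nothing provides for masking.
- **Operator dependence is not stated.** The CT levels are fixed, which limits slice choice, and automated segmentation would reduce reader influence. This also stands. No method is named, so the degree of dependence is unknown in either direction.
- **The analysis is exploratory.** These endpoints are secondary and no confidence interval is specified for them. This limits the weight of step 4, which describes an interval the protocol does not promise. It does not remove the shift from a descriptive mean change.
- **A fixed percentage shift is not demonstrably enough.** One might argue that a 1% reading shift in thigh muscle would create an apparent effect. With assumed SDs of change of 3%, 4% and 5%, the half-width at n = 70 is 0.72%, 0.95% and 1.19%. At 5% the half-width exceeds the shift, and the documents support neither the SDs nor the 1%.

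The 2-week deadline is also generic wording used for most forms, so it was probably not chosen with image reading in mind. Its effect on the order of reading is the same.

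**Conclusion.** The point holds as a cheap improvement. The study is open and uncontrolled, it evaluates before-after change in CT and MRI readings, it has baseline values filed at least 18 weeks before the second scan, and it provides for no masked or paired read. Reader expectation therefore cannot be excluded from the mean changes in liver fat, visceral fat and thigh muscle.

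The stronger conclusion, that such a bias is present or passes with certainty into the results, is not supported: the readers, the reading method and the reading error are all unstated. The size is known only conditionally. It rests on an assumed shift, all 70 patients evaluable, and a t interval for the mean change. The consequence is confined to secondary, exploratory endpoints, although they carry the body-composition part of the objective.

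**What to change.** - **Sections 5.1 and 5.3.** State that the endpoint values for liver fat, visceral fat and thigh muscle are measured from stored images coded to hide name, date and visit. An existing reader measures a patient's scans together, in random order. Someone other than the reader holds the code.
- **Patients without a post-test scan.** Read their baseline scans in the same masked batch. Otherwise their baseline values would be lost to the modelling of adherence on baseline factors in 11.2.3, where patients who drop out matter. A lone scan may be recognizable as a baseline, but no change is computed from it.
- **Section 12.1.** Move the due date of form 4 to after the masked read.

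**Cost.** Some image-coding work, and imaging endpoint values that arrive later. No extra scan or visit is needed. The protocol names no reader, so it is an assumption that one is already available. Section 18.2 justifies the participants' share of the imaging cost by what they learn about their own condition. Any results given to them for that purpose can be handled separately, since only the endpoint value has to come from the masked read.

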5.4. Provisions for concomitant medications (concomitant therapy)

## None

## 5.5. Criteria for stopping exercise therapy

1 Severe complications (motility disorders, hypoglycemia, hypotension) occur.

2 If an attending physician judges that continuation of the exercise therapy is difficult.

3 Criteria for discontinuation of study treatment

（1）When the individual subject of the research withdraws his/her consent.

（2）If it becomes impossible to continue the study treatment due to the occurrence of adverse events, etc.

（3）If found to be ineligible case.

（4）If the subject does not come to the hospital due to relocation, etc.

（5）If the study physician determines that the study should be discontinued.

（6）If the study is discontinued.

※ Temporary interruption of study is not considered a discontinuation, and study will be resumed as soon as it can be resumed.

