# 7. Endpoint

## 7.1.　 Primary endpoint

## Percentage change in HbA1c at the beginning of the study and at 20 weeks.

## 7.2.　 Secondary endpoints: Liver fat mass by MRI, abdominal visceral fat and thigh muscle mass by CT, thigh muscle strength by EMG, BMI, VO2 peak (maximal oxygen uptake), insulin sensitivity (blood C-peptide, IRI), HDL cholesterol, LDL cholesterol, triglycerides, systolic blood pressure, mean blood glucose and variability (using FreeStyle Libre Pro), urinary albumin, changes in drug dosage from baseline (start) to 20 weeks (end for some items), frequency of IWT and target achievement rate (at least 60 minutes/week of fast walking).

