8.2.　 Beginning and End Endpoints

・Body composition evaluation: liver fat content by abdominal MRI, abdominal visceral fat content by CT, thigh muscle mass by CT.

・Thigh muscle strength using isometric lower limb muscle testing equipment.

・Physical fitness measurement (using of JD Mate): VO2 peak (maximum oxygen uptake), target level value for training, maximum heart rate.

・Mean blood glucose and blood glucose variability（using of FreeStyle Libre Pro）

・Daily calorie consumption (using of JD Mate): calorie consumption, number of steps, measurement time (minutes)

・Dietary survey

・Concomitant medications: changes from start to end of diabetes medications (insulin, oral medications), hypertension medications, and lipid disorder medications.

・Insulin sensitivity*: blood CPR, IRI

・Blood tests*: HDL-C, LDL-C, triglycerides, BUN, Cre, eGFR, AST, ALT, fasting blood glucose, HbA1c.

・Urinalysis*: Urinary albumin (creatinine equivalent)

・Vital signs*: systolic and diastolic blood pressure.

・Body weight *

　*…Also evaluate at 4, 8, 12, 16, and 18 week visits.

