8.4.　 Post-End Assessment Items

・Surveys for adverse events (collected only for hypoglycemia and hypotension), serious adverse events (SAEs), and locomotor disorders.

Observation, Inspection and Reporting Schedule

|  | **screening** | **previous observation** | **Start Date** | **4 w** | **8w** | **12w** | **16w** | **18w** | **20w** | **after the end** | **time of cessation** |
| --- | --- | --- | --- | --- | --- | --- | --- | --- | --- | --- | --- |
|  |  |  | **baseline** | **±2w** | **±2w** | **±2w** | **-2w　+1ｗ** | **±1w** | **±2w** | **The items implemented from 20 weeks to 28 weeks of the start date.** |  |
| Patient Background | ○ |  |  |  |  |  |  |  |  |  |  |
| Body Composition Assessment |  | ○ |  |  |  |  |  |  |  | ○ |  |
| Physical fitness test |  | ○ |  |  |  |  |  |  |  | ○ |  |
| Interval fast walking |  |  |  |  |  | （20ｗ+ Until the end） |  |  |  |  |  |
| Dietary survey | ○ |  |  |  |  |  |  | ○ |  |  |  |
| Calorie consumption | ○(1w) |  |  |  |  |  |  | ○(1w) |  |  |  |
| BMI | ○ |  | ○ |  | ○ | ○ | ○ |  | ○ |  | (Weight only) |
| Insulin sensitivity |  |  | ○ |  |  |  |  |  | ○ |  |  |
| Blood test | ○ |  | ○ | ○ | ○ | ○ | ○ |  | ○ |  |  |
| Urinalysis | ○ |  | ○ |  |  |  |  |  | ○ |  |  |
| Blood pressure | ○ |  | ○ | ○ | ○ | ○ | ○ |  | ○ |  | ○ |
| Blood glucose level variation | ○(2w) |  |  |  |  |  |  | ○  (18~20w) | |  |  |
| concomitant medications |  |  | ○ |  |  |  |  |  | ○ |  | ○ |
| Survey on locomoter disorders |  |  | ○ | ○ | ○ | ○ | ○ | ○ | ○ | ○ | ○ |
| Adverse events |  |  |  |  |  |  |  |  |  | ○ | ○ |

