### 3）Safety analysis set (SAF): population of participants who have received at least one protocol treatment.

### 11.2.2.　 Analysis on the primary endpoint (analysis population: FAS)

The percent change in HbA1c from baseline (start date) to 20 weeks in subject i is defined as follows. If HbA1c measurements at either or both time points are missing, the rate of change in HbA1c is considered missing.

$${HbA1c rate of Variation}_{i}=\frac{{HbA1c measurements}_{i,baseline}-{HbA1c measurements}_{i,20w}}{{HbA1c measurements}_{i,baseline}}$$

Estimate the mean and 95% confidence interval of the mean for the rate of change in HbA1c.

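### Week-20 HbA1c is not secured in participants who stop interval walking training (IWT) without withdrawing consent

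*Protocol*

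**What the plan says.** The primary endpoint in section 7.1 is "Percentage change in HbA1c at the beginning of the study and at 20 weeks". Section 11.2.2 computes it from the baseline and week-20 values alone, in the full analysis set (FAS), and adds: "If HbA1c measurements at either or both time points are missing, the rate of change in HbA1c is considered missing". HbA1c is measured as part of the blood test item, whose list in section 8.2 ends "triglycerides, BUN, Cre, eGFR, AST, ALT, fasting blood glucose, HbA1c".

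On participants who do not carry the training through, the text is spread over four places.

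- Section 5.3 says that adherence is of interest and so, "except for participants who withdraw their consent, the study will continue even if the actual fast walking time is not enough". It goes on: "Eventually, all remaining participants will be evaluated after completion of the study".
- Section 5.5 is headed as criteria for stopping exercise. Its third item lists six grounds for discontinuing study treatment, including "If it becomes impossible to continue the study treatment due to the occurrence of adverse events, etc". Other grounds are withdrawal of consent, ineligibility, non-attendance and a physician's decision that the study itself should end for that participant. Temporary interruption is expressly not discontinuation.
- The schedule in section 8.4 has a separate time-of-cessation column.
- Section 12.1 has one discontinuation form for both situations, due "Within 2 weeks of treatment discontinuation or dropout".

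**The concern.** Take a participant who stops walking for good at week 6 because of joint pain, does not withdraw consent, and still comes to the hospital for diabetes care. Section 5.3 suggests that this person stays in and is evaluated at the end. Section 5.5 and the schedule suggest discontinuation with a cessation visit at which no HbA1c is drawn. A site cannot tell from the protocol which applies.

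The primary outcome in a selected group is at stake. People who stop because of harm or difficulty plausibly improve less than those who carry on. In a single-arm study no control group would show the same loss, so selective loss goes straight into the reported mean. What is collected after stopping has to be settled in the protocol, because an analysis plan cannot restore a week-20 value that was not drawn.

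**Working it through.** **Step 1: the schedule, column by column.** The table has 11 columns.

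| Row | Marked at | Time of cessation |
| --- | --- | --- |
| Blood test (HbA1c) | screening, start, weeks 4, 8, 12, 16, 20 (7 of 11) | blank |
| "Blood pressure" | the same seven columns, plus cessation | marked |
| BMI | several visits | weight only |
| Concomitant medications | start, week 20 | marked |
| Locomotor survey, adverse events | various | marked |
| Insulin sensitivity, urinalysis, body composition, fitness | various | blank |

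The blood pressure row shows that the last column is being read correctly. Cessation has its own assessment set, and the primary variable is not in it.

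**Step 2: is the week-20 visit kept after stopping?** No sentence in sections 5.3, 5.5, 8 or 12.1 says that it is, and none says that it is dropped. The 20-week column exempts nobody.

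**Step 3: consequence in the analysis.** A stopper with a baseline value can belong to the FAS, but without a week-20 HbA1c the rate of change is missing under section 11.2.2. The mean and its 95% confidence interval then rest on those measured at week 20.

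**Step 4: size, as an illustration.** The plan has no figure to reproduce: the target of 70 rests on feasibility, and no dropout rate or expected change is given. Assume that a share p has no week-20 HbA1c, with mean relative reduction m_c in completers and m_s in stoppers.

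- Mean in all starters = (1 − p)·m_c + p·m_s
- Bias of the completers' mean = p·(m_c − m_s)
- With m_s = 0, overstatement factor = 1/(1 − p)
- Confidence-interval width ratio = √(70/(70 − number lost)), for the same standard deviation

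| p | Lost / left | 1/(1 − p) | Width ratio |
| --- | --- | --- | --- |
| 10% | 7 / 63 | 1/0.90 = 1.11 | √(70/63) = 1.05 |
| 20% | 14 / 56 | 1/0.80 = 1.25 | √(70/56) = 1.12 |

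In absolute terms, if completers improve by an assumed 3% to 6% of baseline and stoppers not at all, the mean in all starters is 2.7% to 5.4% at p = 10% (bias 0.3 to 0.6 percentage points). At p = 20% it is 2.4% to 4.8% (bias 0.6 to 1.2 points).

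The result depends on m_s. If stoppers worsen by 3%, the overstatement is 18% to 25% at p = 10% and 43% to 67% at p = 20%. If stoppers change as completers do, there is no bias and only precision is lost.

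**The case against.** The best defence is that the protocol can be read so that nothing is lost. The relevant headings in section 5.5 speak of exercise and study treatment, the 20-week column applies to everyone, and section 5.3 promises to evaluate all who remain. On that reading a stopper who has not withdrawn consent is simply seen at week 20. This is a permitted reading. It stands against any claim that HbA1c is never collected after stopping, which a reader might infer from the blank cell. It does not remove the ambiguity, because the only column written for stoppers omits the blood test.

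Three other strong readings are not supported.

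- A reader might take section 5.3 to say that only withdrawal of consent removes a participant, in flat contradiction of section 5.5. The sentence concerns insufficient fast-walking time, and the next one already assumes that some participants leave.
- A reader might turn the 17% locomotor disorders in section 9.4 into about 12 of 70 stopping. That is an event frequency from a cited exercise study, not a stopping rate.
- A reader might conclude that the relation between amount of IWT and reaching HbA1c below 7% loses its low end. Section 5.3 deliberately keeps low adherers, so at most some formal stoppers are missing from it.

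It is also fair that not every ground matters equally: someone who has moved away cannot readily be measured at week 20, and closure of the whole study is not selective. The problem lies mainly with adverse events and physician decisions. HbA1c from weeks 4 to 16 may exist for later stoppers and could support a sensitivity analysis, though the stated endpoint does not use it. Finally, the study is exploratory and estimates a mean without a decision threshold, which limits the consequence but not the direction of the likely bias.

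**Conclusion.** The point holds as a gap in data collection. The protocol does not state whether week-20 HbA1c is taken from participants who stop IWT but have not withdrawn consent, and its schedule leans towards not taking it. If that is how sites act, the primary estimate describes completers and is probably too favourable.

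The 11% to 25% overstatement rests on three assumptions: 10% to 20% stop, none of them has a week-20 value, and their mean change is zero. The protocol confirms none of these, so the figure shows the order of size and is not a prediction. That the gap exists does not depend on them.

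**What to change.** Reconcile sections 5.3, 5.5 and 12.1 and the schedule.

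- In section 5.5, separate stopping IWT from leaving the study or withdrawing consent, and record the two separately on the discontinuation form in section 12.1.
- State that participants who stop IWT, do not withdraw consent and can still attend keep the already scheduled week-20 blood test (HbA1c) and concomitant-drug record, and that these values enter the FAS primary analysis.
- Make clear in the schedule that the cessation column does not replace the 20-week column for these participants.
- Optionally, mark the blood test at cessation for those who will not return. Section 11.2.2 would not use that value, so it would serve a sensitivity analysis only.

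The cost is a short amendment, approved by the ethics committee as section 17 requires, and at most one routine blood test per participant concerned. The week-20 test is already planned. The change concerns only what is measured after stopping and takes no view on when exercise should be stopped.
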